Multiple attempts have been made at evaluating the degree of organ damage and capability to recover function after LT. From the original definition of early allograft dysfunction (EAD) by Olthoff et al. [14, 15], through the model for early allograft function (MEAF) score by Pareja et al. [6] a new category of scores based on the kinetics of multiple parameters have recently emerged. Two scores, one developed in the United States at UCLA (L-GrAFT) [1] and one in Italy from a multicenter cohort (EASE) [2], allow the prediction of early AF with excellent C-statistics. Both were validated on multicentric external populations [16, 17]. L-GrAFT and EASE scores are calculated at day 10 after LT; furthermore, a modification of the L-GrAFT score, calculated at day 7, was subsequently developed and validated [17]. Both scores are also proposed for quantifying the degree of graft recovery in translational studies [18–20]. A synopsis of the characteristics of the different scores is displayed in Table 1. However, the prognostic role of pretransplant graft macrosteatosis, the differences among phenotypic patterns of various transplant types (DBD, DCD, and living donor grafts), as well as the detailed characterization of the dynamics that make retransplantation sustainable or contraindicated have not been investigated [21, 22]. Prospective studies evaluating these endpoints and further mitigation strategies to reduce graft-related risks are still awaited.

**Table 1 Tab1:** Previous scores (object, endpoint, cutoff, number of factors utilized, number of entries, accuracy, discrimination power, strength and limitations)

	DRI (2006) [9]	EAD (2010) [5]	D-MELD (2011) [18]	New ET-DRI (2012) [19]	SOFT (2008) [20]	MEAF (2015) [6]	L-GrAFT (2018) [1]	L-GrAFT (2021) [15]	EASE (2020) [2]
Object of score	Donor quality	Graft quality	Donor–recipient match	Donor quality	Donor–recipient match	Graft recovery	Graft recovery	Graft recovery	Graft recovery
Origin of data	UNOS registry data	3 centers	20 centers	EURO TRANSPLANT registry data	UNOS	Monocentric	1 Center	7 Centers	16 Centers
*N* of patients (developing set)	20,023 1998–2002	297 2004–2005	3281 2002–2009	5723 2003–2007	21,673 2002–2006	1026			
Endpoint	Graft failure	Graft dysfunction	Graft failure/patient death	Graft failure	Patient death	Graft failure	Graft failure	Graft failure	Graft failure

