#### Study size and power calculations

The study size was calculated to achieve adequate statistical power for the development and validation of prognostic algorithms. Calculations were independently performed by the G-Step Statistical Facility of the Fondazione Policlinico A. Gemelli IRCCS.

*1. Prior knowledge*

1.1. AF incidenceIncidence of allograft failure (AF) at 90 days according to the L-GrAFT study (2018): 11.1% [1].Incidence of AF at 90 days according to the EASE score study: 6.7% [2]—Incidence of EAF according to the L-GrAFT validation study (2020) in UCLA: 7% [17].Incidence of AF at 90 days according to the L-GrAFT validation study (2020) in other US validation centers: 11% [17].Incidence of AF at 90 days according to the L-GrAFT validation study (2020) in European COPE cohort: 4% [17]. Notably, the COPE cohort consists of 222 grafts.

Research hypothesis stratified by donor category:10% AF in liver transplantation with high-risk deceased donors;7% AF in liver transplantation with standard deceased donors;4% AF in liver transplantation with living donors.

1.2. EASE and L-GrAFT score performance as AUC (95% confidence interval)EASE(10) AUC = 0.87 (0.83, 0.91).L-GrAFT10 AUC = 0.72 (0.65, 0.78).L-GrAFT7 AUC = 0.78 (0.75, 0.82).

*2. L-GrAFT and EASE score algorithms validation*

Current target sample size (*n*):5000 transplants overall;> 4125 for the retrospective study.750 for the prospective study.

This estimation aims to provide the minimum sample size to achieve the baseline AUC, considering a different AF incidence for each donor category. The baseline (i.e., lowest) AUC = 0.72 of the L-GrAFT10 score is considered a minimum performance requirement to reach a conservative sample size estimation.

Assuming an overall AF rate of 6% and aiming to exclude an AUC value of 0.72, a minimum sample size of 4000 patients will result in a 95% confidence interval width of 0.072; so, if we obtain an AUC of at least 0.76, the 95% confidence interval, ranging from 0.724 and 0.796, will allow to exclude the value of 0.72.

*3. Dimension of the validation set.*

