Kaplan–Meier curves will be calculated and differences will be investigated through log-rank test.ii.Missing data management.

A. Missing data in the calculation of the area under the curve (AUC) and the slope of the kinetic model will be addressed as follows:Patients who were retransplanted or died before day 10 were excluded from the calculation of the AUC and slope because of the real impossibility to calculate the score which is by definition computed at day 10. The number of this subgroup will be reported in the flow diagram of the patients. These cases will be excluded from the patient population utilized for the development of algorithms. However, these cases will be considered for the calculation of the outcome measures (overall % of AF, % failure at 90 days, % failure at 365 days, length of stay, overall graft survival, and overall patient survival).Patients who have been discharged between day 8 and 10 and do not have the day 10 determination (missing value referring to the day 10 determination of AST or Platelet count or bilirubin). In these cases, the values at day 7 will be used. The number of these cases will be reported in the flow diagram. We are aware that this approach might overestimate the value of the AUC and consequently the score’s value. However, as the number of patients without day-10 data is expected to be small, we believe that the effect will be minimal and not relevant for the purpose of the study.Patients with missing data at day 2, or day 3 will be excluded, being impossible the calculation of the score. Their number will be reported in the flow diagram.Patients with missing data at day 4 will be included. The AUC and the slope will be calculated using the trapezoid method not including day 4. Their number will be reported in the flow diagram.Patients with missing data at day 5 will be included. The AUC and the slope will be calculated using the trapezoid method not including day 5. Their number will be reported in the flow diagram.Patients with missing data at day 6 will be included. The AUC and the slope will be calculated using the trapezoid method not including day 6. Their number will be reported in the flow diagram.Patients with missing data on two consecutive days (day 4 and 5, or day 5 and 6, or day 6 and 7) will be included. The AUC and the slope will be calculated using the trapezoid method not including the two consecutive missing days. Their number will be reported in the flow diagram.Composite missing data (e.g., AST from one day and bilirubin from a different day) will follow the above-mentioned rule. Their number will be reported in the flow diagram.Missing data in the descriptive analysis will be reported. Parameters of interest with percentage of missings higher than 8% will not be reported in tables neither will be considered for further univariate or multivariate analysis.Loss to follow-up.

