## Discussion

This protocol refers to the first global study on liver transplantation outcomes. The study design includes several objectives based on LT practice worldwide, with centers participating in a balanced manner depending on their country’s location and activity. In addition to cross-sectional information, we expect to acquire a large volume of data to develop new models for predicting AF at different time points.

First, it will be paramount to build a new model for predicting early AF (i.e., 90-day post-LT allograft failure) based on a multicenter international comprehensive retrospective and prospective data collection. The work set by the steering committee stands on the background of the existing kinetics-based scores (L-GrAFT and EASE) constructed from a single center and a multicenter two-nation setting, respectively. Compared to these two scores, the models we aim to develop imply the advantage of a wider setting (60 centers, 21 countries, from 6 world areas) and a prospective patient enrollment. In addition to standard transplant outcome measures (graft failure and patient death at 90 and 365 days), we will pay attention to hospital and ITU length of stay, the incidence of weaning/extubation failure [57], as well as surgical complications. [58–60] Furthermore, we expect the study to allow us to develop and validate model(s) with increasing predictive accuracy from the 3rd to 7th postoperative day, making them more usable for all-day practice, bringing forward the availability of prognostic tools in the first few days after LT. We expect these tools to be able to weigh the risk of death without retransplantation and aid the decision-making processes for transplant physicians.

The presence of a retrospective study segment composed of high- and medium-volume centers guarantees a second-layer control of the applicability of previous models as well as the potential backward test of new models to real-world scenarios. The existing kinetic-based scores will be tested on the retrospective data with the aim of validating them on a large scale on a broad variety of liver transplant centers across different countries.

Second, we extended the evaluation time to 365 days, with the intent of capturing those failures occurring at a later stage. Late failure is increasingly seen nowadays due to the growing utilization of DCD and ECD grafts and the subsequent loss of grafts from ischemic cholangiopathy.

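### The rule for two consecutive missing days treats a gap at days 6 and 7 as interior; for a score that ends at day 7 it cuts the area under the marker curve at day 5

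*Protocol article*

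**What the plan says.** The rules stand in the protocol article, Statistical analysis plan, item ii (Missing data management). They cover the area under the curve and the slope of the kinetic model. Here AUC means the area under a marker's daily curve, not the C-statistic.

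- Patients with gaps on two successive days are kept: "day 4 and 5, or day 5 and 6, or day 6 and 7) will be included". For them, "The AUC and the slope will be calculated using the trapezoid method not including the two consecutive missing days". No closing day, rescaling or imputation is named, and the pair 6-7 is handled exactly like 4-5 and 5-6.
- Single missing days 4, 5 and 6 each have a rule. A missing day 7 on its own has none.
- Patients discharged between days 8 and 10 without a day-10 determination have a substitution rule: "In these cases, the values at day 7 will be used".
- Patients missing day 2 or day 3 are excluded because the score cannot be calculated.
- Early deaths and retransplants are left out because of "the real impossibility to calculate the score which is by definition computed at day 10".

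On the scores themselves, the Introduction says "L-GrAFT and EASE scores are calculated at day 10 after LT" and adds that "a modification of the L-GrAFT score, calculated at day 7, was subsequently developed and validated". Table 1 gives the 2021 L-GrAFT an evaluation time of 7 days. The sample size section lists its C-statistic as prior knowledge: "L-GrAFT7 AUC = 0.78 (0.75, 0.82". The Discussion expects "model(s) with increasing predictive accuracy from the 3rd to 7th postoperative day", in line with secondary objective #4.

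**The concern.** A trapezoid sum tolerates a missing interior day, because the next observed day closes the gap with a straight line. It does not tolerate a missing last day: the integral simply ends early. The rule lists three pairs of days as if they were alike. They are alike for a window that runs to day 10. For a window that ends at day 7, the third pair is the end of the window.

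Validation of the existing kinetic scores is an aim of the study, and L-GrAFT7 is one of them. A patient scored on days 1 to 5 and read against a formula built on days 1 to 7 contributes a value on a different scale. Such values enter the validation as if they were ordinary scores.

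A second problem follows from the same rule. It admits patients without a day-7 value, while the early-discharge rule relies on that value.

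**Working it through.** The protocol gives no figure for the effect of this rule, so there is none to reproduce. The check compares the trapezoid area with and without the missing days.

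**Inputs**
- From the protocol: the pair rule, the trapezoid method and the day-7 and day-10 evaluation times.
- Assumed: one value per day from day 1. Table 1 is consistent with this for the day-10 L-GrAFT (40 determinations over 4 variables, 40/4 = 10 each).
- Assumed: the marker shapes below. The protocol gives none.

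**Formula.** Area = sum over successive observed days of (day gap) x (mean of the two values).

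**Window ending at day 7, days 6 and 7 missing.** Days 1 to 7 hold six intervals and days 1 to 5 hold four.

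| Shape | Area, days 1-7 | Area under the rule | Error | Day 5 carried to day 7 | Error |
|---|---|---|---|---|---|
| Flat at 1 | 6 | 4 | -33.3% | 4 + 2 x 1 = 6 | 0% |
| Linear fall 6 to 2 (day 5 = 3.33) | 6 x (6+2)/2 = 24 | 4 x (6+3.33)/2 = 18.67 | -22.2% | 18.67 + 2 x 3.33 = 25.33 | +5.6% |
| Linear rise 3 to 9 (day 5 = 7) | 6 x (3+9)/2 = 36 | 4 x (3+7)/2 = 20 | -44.4% | 20 + 2 x 7 = 34 | -5.6% |
| Halving daily from 1 (day 5 = 0.0625) | 1.477 | 1.406 | -4.8% | 1.406 + 2 x 0.0625 = 1.531 | +3.7% |

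A further set of shapes gives -13.9% (falling about 30% per day), -26.6% (falling 10% per day) and -39.8% (rising 10% per day).

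**Interior gaps, for comparison.** For the flat shape and that further set, in the same day-7 window, missing days 4-5, 5-6 or 6 alone changes the area by 0% to +3.0%.

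**Window ending at day 10, days 6 and 7 missing, day 8 observed.** The gap is bridged from day 5 to day 8. In the same shapes the error is 0% to +1.4%, so nothing is truncated.

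**Direction of the score.** The coefficients are not in the protocol, and platelets are among the main parameters in Table 3. A toy score was taken as the sum of ln(area) for AST, bilirubin and INR, minus w times ln(area) for platelets. With AST falling about 30% per day, bilirubin 5%, INR 7%, and platelets rising 10%, truncation changes ln(area) by -0.149, -0.356, -0.337 and -0.508. The change in score is therefore -0.843 + 0.508 x w:

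| w | 0 | 1 | 1.5 | 2 | 3 |
|---|---|---|---|---|---|
| Change in score | -0.84 | -0.34 | -0.08 | +0.17 | +0.68 |

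The sign turns at w = 0.843/0.508, about 1.66. The slope is not shortened in the same way, but it does shift for curved profiles: a straight-line fit on days 1-5 against days 1-7 gives -0.188 against -0.141 for the steep fall, and 0.116 against 0.128 for the rise.

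**The two rules together.** Take a patient missing days 6 and 7, discharged between days 8 and 10, with no day-10 value. The pair rule keeps this patient. The discharge rule asks for the day-7 value, which does not exist. In the limiting case where nothing after day 5 is observed and the sum simply stops, four of nine intervals remain. The area of a day-10 score is then 20.8% to 65.8% too small for the flat shape and the further set. The protocol does not say that it would proceed this way; it gives no outcome for this patient.

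**The case against.** The best case against the point is that the section is written for day-10 scores. It says that its score is defined at day 10, and its discharge rule is about a day-10 determination. In that window days 6 and 7 are interior, and the rule works. A separate rule for L-GrAFT7 could sit in a fuller plan. This stands in part: the rule is sound for the score that the section has in view, provided a later value exists. But the rules are introduced for the kinetic model generally and are not confined to day-10 scores, while the protocol names L-GrAFT7 elsewhere. A programmer who follows the text literally would truncate.

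A reader might also infer that affected patients get a falsely low score, so that failing grafts are pushed towards low risk. The protocol does not support that. It links a larger area to a larger score only when discussing the day-10 substitution, and it gives no coefficients. If platelets count as protective, their truncated area pushes the score up. Distorted discrimination or calibration has not been shown either: the errors computed are in single-marker areas.

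Nor can the point be pressed against objective #4 as such. The protocol does not say that the new day-3-to-7 algorithms will use a trapezoid area, and they have no fixed coefficients yet. They are touched only if they adopt that construction.

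The clash with the discharge rule is a missing input, not two conflicting values, and it needs an unusual combination of gaps. Finally, exclusion of patients who died or were retransplanted before day 10 reduces the exposure, and the promised flow-diagram counts will make it visible. Neither corrects the value assigned to those who remain.

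**Conclusion.** The point holds in a limited form. The rule does not separate terminal from interior gaps. Applied to L-GrAFT7, or to any new day-7 model built on a trapezoid area, it integrates to day 5 only. The area is about 5% to 44% too small across the assumed shapes, against at most about 3% for interior gaps in the shapes tried. The score is then not comparable with one built on days 1 to 7.

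Separately, the protocol keeps some patients for whom its own day-7-for-day-10 substitution has no input.

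The size rests on assumed daily values and marker shapes. The direction of the score error and the number of patients affected cannot be derived from the protocol. For day-10 scores with a later observed value there is no material problem.

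**What to change.** Add one sentence to the missing-data rules: missing days are bridged only when a later observed day within the window of the score in question closes the gap. Where none does (day 7 missing for a day-7 score, alone or with day 6; or days 7 and 10 both missing for a day-10 score), either impute the terminal value from the earlier days and the other markers, or declare that score not computable and count the patient in the flow diagram. The second option follows what the section already does for days 2 and 3. The sentence also settles the case that the discharge rule leaves open, and the case of day 7 missing alone.

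The cost is that sentence and a small change to the score code. A few patients will be imputed or will drop out of that score. Carrying day 5 forward, shown above within about 6%, only illustrates how far a simple completion narrows the error; the choice of imputation method remains open.

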## Discussion

This protocol refers to the first global study on liver transplantation outcomes. The study design includes several objectives based on LT practice worldwide, with centers participating in a balanced manner depending on their country’s location and activity. In addition to cross-sectional information, we expect to acquire a large volume of data to develop new models for predicting AF at different time points.

First, it will be paramount to build a new model for predicting early AF (i.e., 90-day post-LT allograft failure) based on a multicenter international comprehensive retrospective and prospective data collection. The work set by the steering committee stands on the background of the existing kinetics-based scores (L-GrAFT and EASE) constructed from a single center and a multicenter two-nation setting, respectively. Compared to these two scores, the models we aim to develop imply the advantage of a wider setting (60 centers, 21 countries, from 6 world areas) and a prospective patient enrollment. In addition to standard transplant outcome measures (graft failure and patient death at 90 and 365 days), we will pay attention to hospital and ITU length of stay, the incidence of weaning/extubation failure [57], as well as surgical complications. [58–60] Furthermore, we expect the study to allow us to develop and validate model(s) with increasing predictive accuracy from the 3rd to 7th postoperative day, making them more usable for all-day practice, bringing forward the availability of prognostic tools in the first few days after LT. We expect these tools to be able to weigh the risk of death without retransplantation and aid the decision-making processes for transplant physicians.

The presence of a retrospective study segment composed of high- and medium-volume centers guarantees a second-layer control of the applicability of previous models as well as the potential backward test of new models to real-world scenarios. The existing kinetic-based scores will be tested on the retrospective data with the aim of validating them on a large scale on a broad variety of liver transplant centers across different countries.

Second, we extended the evaluation time to 365 days, with the intent of capturing those failures occurring at a later stage. Late failure is increasingly seen nowadays due to the growing utilization of DCD and ECD grafts and the subsequent loss of grafts from ischemic cholangiopathy.

Finally, the balanced data enrollment (each center in the prospective or retrospective segment will enroll a fixed number of cases) constitutes the best solution to minimize the center-volume effect bias.

The predictive models we aim to develop would also be tailored to the changing composition of the donor pool, with an emphasis on DCD, ECD, and possible risk-mitigation strategies. Such strategies, mainly machine perfusion (MP) but also minimizing donor hepatectomy time, warm and cold ischemia time, are heterogeneously implemented in the participating centers. This will also describe the current management options and provide a snapshot of the differences in clinical practice across the centers. Since the study enrollment encompasses 7 years, including 2 years of variable LT activity due to the COVID-19 pandemic, the growing adoption of MP translates into more frequent usage in the prospective study segment. This potential bias will be taken into account in all the statistical analyses. As MP for DCD and risky DBD grafts keeps gaining momentum and more trials are coming, our study will parallel the evolving scenario of graft reconditioning and extended preservation. Differently from most studies, [61, 62], we expect to enroll more DCD and DBD cases treated with MP in both study segments. Furthermore, the global perspective of the study will allow for a deeper analysis of the mitigation effect of MP, also about center volume. Nevertheless, we are aware that since this study remains observational, novel experimental procedures such as MP-based pharmacological defatting [63] will not be incorporated.

With an all-round evaluation of the LT candidate (including frailty, nutritional status, and comorbidities), we plan to acquire data on the background condition of the recipients and stratify those risk factors that, together with intraoperative, graft histology and postoperative factors interact with each other in the generation of the transplant outcome. Gender disparity and female penalization in access to LT will also be measured and potential corrections be explored. Postoperative events and complications will be recorded, and their effect will be weighed to analyze their impact on the indication for retransplantation (e.g., when is retransplantation sustainable? How do we define the boundary of futility?) Finally, as the follow-up continues to extend, we can identify predictors of the primary disease's medium- and long-term recurrence and the development of lymphomas and epithelial neoplasms. [64].

In conclusion, the IMPROVEMENT Study will provide a large amount of data for extrapolating conclusions on various aspects in the field of liver transplant outcome prediction. It will focus on contraindications and timing of retransplantation, resource allocation, and the effect of risk-mitigation strategies, as well as the development of ischemic cholangiopathy.

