**Fig. 3 Fig3:**
[figure not shown]
Rank of countries according to liver transplant activity and rank of enrolled transplants

The study will be structured in two segments, based on the enrollment modality: prospective and retrospective. Two distinct data collections will be created accordingly.Prospective segment. Seven hundred fifty liver transplant recipients will be enrolled in 15 high-volume centers (defined as performing ≥ 65 LT a year on average during the 2017–2019 period). Each center will enroll 50 consecutive transplants from July 2021 to December 2023 according to the inclusion criteria. For each transplant, a further 365 days will be necessary for the minimum follow-up.Retrospective segment. A retrospective data collection was conceived for medium–low volume centers (defined as performing < 65 LT a year), to participate in the study using the data of LTs performed between December 31, 2019, and January 1, 2017 (75 cases backward enrollment).

High-volume centers participating in the prospective segment will be allowed to enroll patients in the retrospective segment, too, voluntarily, thus enrolling 125 transplants (50 prospective and 75 retrospective transplants).

Inclusion and exclusion criteria are depicted in Table 4.

**Table 4 Tab4:** Inclusion and exclusion criteria

Inclusion criteria
1. Adult cases (≥ 18 years) 2. First transplant (retransplants to be enrolled when first transplant enrolled) 3. DBD grafts 4. DCD grafts (controlled and uncontrolled) 5. DBD and DCD grafts managed by perfusion machines 6. Living donor grafts (both left lobe and right lobe grafts) transplanted into adult recipients 7. Split liver grafts (both left lobe and right lobe grafts) transplanted into adult recipients
Exclusion criteria
1. Combined grafts (e.g., liver-kidney, liver-heart, liver-pancreas, multi-visceral grafts) 2. Domino grafts 3. Heterotopic grafts 4. Double grafts 5. Cholangiocarcinoma 6. Colorectal liver metastases

Due to some concerns regarding the differences in the prevalences of AB0 incompatible grafts among different countries, these patients can be enrolled concurring to the target number of cases for each center. During the statistical analysis, we will evaluate the opportunity to include them or not in the study population, being aware of the substantial equivalence in the survival results

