### Statistical analysis plan

First, a cumulative incidence of allograft failure will be calculated. To define the best time for retransplant, different strategies may be implemented, based on the collected data at study end. As first choice, we will first draw a Kaplan–Meier for each risk stratum (i.e., each graft subtype). Then, we will analyze all potential risk factors for AF in each subtype by univariate and multivariate Cox regression models. Finally, we will implement these results in a temporal algorithm based on Cox curves to identify potential time windows for retransplant. In the case of multiple drops in the initial KM curves of similar duration, we will build the algorithm so to uniform the duration of each time-window. Alternatively, we can implement a change-point analysis model derived from Kaplan–Meier estimation of the survival function followed by the least-squares estimation of the change point [51], or a wavelet analysis of change-points based on a non-parametric hazard model [52]. We could also determine the different time windows by using an extension of Glazer’s method, using a mixture of two gamma distributions, hypothesizing two or more turning points [53]. Another possibility is represented using a Bayesian approach to the problem of hazard change with unknown multiple change-points by implementing a stochastic approximation Monte Carlo algorithm for efficient calculation of the posterior distributions [54]. Particularly used in graft failure prediction. Also, a joint latent change-point class model could represent a potential way to improve the prediction of fixed time windows for retransplantation [55, 56]. All these potential applications would depend on the data distribution at the end of data collection and events observed during the follow-up period.

Notably, since the percentage of adoption of machine perfusion is expected to be one of the main differences between the two study segments, although heterogeneously worldwide, models will be adjusted according to this parameter.i.Subgroups and interactions.

The incidence of AF at 90 and 365 as well as the incidence of death at 90 and 365 days will be calculated. Differences between the three main graft types subgroups will be investigated using either one-way ANOVA, if normally distributed, or otherwise by the Kruskal–Wallis non-parametric test. The Chi-square test will instead assess differences between qualitative variables. The significance level will be set at < 0.05.

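### Fixed case quotas only equalise centre weights: the planned precision still assumes independent patients, and the graft-type and perfusion comparisons stay open to confounding by centre, volume and period

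*Protocol article*

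**What the plan says.** **Design (Setting, Table 3).** In the prospective segment, 15 centres performing at least 65 transplants a year take part: "Each center will enroll 50 consecutive transplants from July 2021 to December 2023". The retrospective segment is meant for centres below 65 a year, with "75 cases backward enrollment" from 2017–2019; Table 3 plans 56 centres. High-volume centres may join it voluntarily, "thus enrolling 125 transplants (50 prospective and 75 retrospective transplants".

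**Claim (Discussion).** The fixed number per centre "constitutes the best solution to minimize the center-volume effect bias". The Introduction criticises earlier work for leaving centre volume out of account, although Table 1 marks the EASE score as stratified by centre volume.

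**Precision (Study size and power calculations).** With 6% allograft failure (AF) and 4,000 patients, an AUC of 0.76 is given a 95% interval of 0.724–0.796, said to exclude 0.72. For the validation set, 800 patients are said to give a standard error of log O/E of 0.14.

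**Analysis.** Differences between the three graft types are tested by one-way ANOVA or Kruskal–Wallis. For categorical data, "The Chi-square test will instead assess differences between qualitative variables". For survival, "Kaplan–Meier curves will be calculated and differences will be investigated through log-rank test". For retransplant timing, "we will analyze all potential risk factors for AF in each subtype by univariate and multivariate Cox regression models". On the difference in machine perfusion between segments, "models will be adjusted according to this parameter". Centre is named as an analysis unit only in the exploration of missing data.

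**Acknowledged imbalance.** The section on sources of bias says perfusion is used more often in high-volume centres. The Discussion says its use varies between centres and is more frequent in the prospective segment, and promises to allow for this.

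**The concern.** Giving every centre the same number of cases stops large centres from dominating the pooled data. It does nothing to the relation between volume and outcome, and patients treated by the same team remain correlated. The design also puts volume and period on the same axis: the prospective segment is high-volume and 2021–23, the retrospective one mainly lower-volume and 2017–19.

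Three things are at stake:

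- **Validation.** The intervals for AUC and O/E would be narrower than the data justify, and the AUC claim has almost no margin.
- **Objective #6 (AF by graft type).** An unadjusted contrast mixes the graft with the place and time of its use wherever graft mix differs between centres or segments.
- **Objective #7 (mitigation strategies).** By the article's own account, perfusion follows volume and segment. A perfusion term adjusts other estimates for perfusion; it does not free the perfusion estimate from confounding by volume or period.

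**Working it through.** **1. Reproduce the stated AUC interval.** Inputs: N = 4,000 and 6% AF, so 240 events and 3,760 non-events; AUC A = 0.76. Hanley–McNeil:

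- Q1 = A/(2−A) = 0.6129; Q2 = 2A²/(1+A) = 0.6564; A² = 0.5776
- SE² = [0.1824 + 239 × (0.6129−0.5776) + 3,759 × (0.6564−0.5776)] / (240 × 3,760)
- SE = 0.01838; 1.96 × SE = 0.036; interval 0.724–0.796, width 0.072

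This matches the article and contains no allowance for clustering.

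**2. Reproduce the stated O/E precision.** SE(log O/E) = √[(1−p)/(np)] = √(0.94/48) = 0.140 at n = 800, p = 0.06. This also matches, again for independent patients. (The quoted incidence interval of 0.043–0.077 is the n = 750 result; 800 gives 0.0435–0.0765.)

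**3. Add clustering.** Design effect DE = 1 + (m−1) × ICC, with m = 50 (prospective) or 75 (retrospective). The article gives no ICC, so 0.005–0.02 is an assumption.

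| Assumed ICC | DE, m=50 | SE(log O/E), n=800 | 95% interval for O/E = 1 | DE, m=75 | AUC lower limit if full DE applied |
|---|---|---|---|---|---|
| 0 | 1.00 | 0.140 | 0.76–1.32 | 1.00 | 0.724 |
| 0.005 | 1.25 | 0.156 | 0.74–1.36 | 1.37 | 0.718 |
| 0.01 | 1.49 | 0.171 | 0.72–1.40 | 1.74 | 0.713 |
| 0.02 | 1.98 | 0.197 | 0.68–1.47 | 2.48 | 0.703 |

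The O/E columns are 0.140 × √DE and exp(±1.96 × SE). The AUC column is 0.76 − 0.036 × √DE. It is a rough upper bound on the loss, since clustering need not inflate the variance of an AUC by the full design effect. Under that bound, 0.72 is no longer excluded once 0.036 × √DE exceeds 0.04, that is DE > (0.04/0.036)² = 1.235, or ICC > 0.235/74 ≈ 0.003.

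**4. Graft-type test.** Simulation of the chi-square test across three graft types: 56 centres × 75 patients, 6% AF, a random centre intercept on the logit scale, no true graft effect, 4,000 runs. Two assumed case mixes were used: living-donor grafts concentrated in 10 centres, or the same mix in every centre.

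| Centre SD (logit) | Approx. ICC, 0.06 × 0.94 × SD² | Type I error, concentrated | Type I error, same mix |
|---|---|---|---|
| 0 | 0 | 0.047 | 0.051 |
| 0.2 | 0.002 | 0.060 | 0.048 |
| 0.3 | 0.005 | 0.069 | 0.056 |
| 0.4 | 0.009 | 0.104 | 0.051 |
| 0.6 | 0.020 | 0.167 | 0.052 |

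The inflation depends on how grafts are spread over centres. With an identical mix there is none beyond simulation error.

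**5. Perfusion.** No arithmetic applies. The article says perfusion is commoner in high-volume centres and in the prospective segment. Its one stated cross-segment adjustment is for perfusion. No term for volume, period or centre is stated that would separate the perfusion effect from these.

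**The case against.** The strongest reply is that this is a condensed article. A centre frailty, a robust variance or a full covariate list may stand in an analysis plan that is not shown, so their absence is not an error in itself. That is right, and the point does not rest on it. It rests on what is stated: the claim made for quotas, two precision figures, and a named set of unadjusted tests.

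Other parts of the reply also stand:

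- A reader might infer that the article claims to have solved the centre effect. It says only that quotas minimise centre-volume bias. The fault is calling them the best solution.
- A reader might infer from the subtype Cox models that graft type never enters a model. Those models are given for retransplant timing, and the section on quantitative variables also lists predictors of graft and patient survival without restricting them to a subtype.
- The high-volume prospective cohort is disclosed as a bias. Voluntary retrospective enrolment by high-volume centres partly separates volume from segment.
- The Discussion promises to account for the perfusion imbalance and to look at perfusion in relation to volume. It names no method for volume or period, so the promise narrows the gap without closing it.
- Objective #6 asks for differences in incidence, which unadjusted tests do describe.

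**Conclusion.** The concern holds in a limited form. Quotas equalise centre weights and do no more. The planned AUC and O/E precision assumes independent patients. At n = 800 the standard error of log O/E rises from 0.14 to about 0.156–0.197 for an assumed ICC of 0.005–0.02, and exclusion of an AUC of 0.72 is fragile because its margin is 0.004. The graft-type tests are confounded, and their error rate inflated, only to the extent that graft mix differs by centre, volume or period; the article does not quantify this. For objective #7 the article itself says that perfusion varies with volume and segment.

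Two stronger readings are tempting and not supported:

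- **An ICC taken from the article's five prior AF rates (4–11.1%).** Their spread gives about 0.013. That is variation between cohorts, some multicentre and from different periods, with sampling error included and one US programme apparently counted twice. It is not a between-centre ICC.
- **A nominal 5% test running at 12–16%.** This follows from that 0.013 and applies only to factors constant within a centre, such as country. Graft type can vary within a centre, and with equal mix the error stays near 5%.

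The plan should be changed on these points, but they do not show that its results would be wrong.

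**What to change.** 1. Withdraw or soften the Discussion sentence: say that quotas balance centre weights, and that volume and centre differences are handled in the analysis.
2. Use centre-clustered intervals (robust or centre-level bootstrap) for AUC and O/E, and a centre random effect or shared frailty in the regression models. A centre contributing to both segments should count as one cluster.
3. Keep the unadjusted graft-type tests as description. Beside them, report for objectives #6 and #7 a model with graft type and machine perfusion, adjusted for centre volume, segment or calendar period, and key pre-specified donor and recipient risk factors.
4. Restate the planned AUC and O/E precision over an assumed ICC range, and say at what value 0.72 would no longer be excluded.

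Centre codes and transplant days are already collected, and centre volume defines the segments, so no new data are needed. The cost is analysis wording and somewhat wider intervals. Because volume and period overlap only partly within segments, their separate effects may be estimated imprecisely, and the report should say so.
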